#### Exploratory subgroup analyses

A small number of re-analyses of the primary endpoint analysis of time to resolution will be carried out to include testing the effectiveness of stratified care for those with/without suspected disc-related radicular pain as determined by clinical assessment, and for patients in each of the stratification subgroups (subgroups 1, 2 and 3). Descriptive statistical summaries will be provided through mean/median time to resolution per treatment arm and per patient subgroup (subgroups 1, 2, 3) according to suspected/not suspected disc-related radicular pain. Tests of statistical significance will be through evaluation of 95% interval estimates / p-values for the interaction term for the product of group variable (with/without suspected disc-related radicular pain) by treatment arm within the Cox regression model adjusting for centre, stratification group (stratifying variables), and pain duration.

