### Stratified care model for sciatica

#### Stratification algorithm

We devised an algorithm to identify those sciatica patients likely to need a fast-track referral from primary care to specialist spinal services, and those who are likely to do well with treatments available in primary care. This algorithm was based on data analysis from the ATLAS study cohort [20] which provided information on the characteristics of sciatica patients most likely to be referred to spinal specialist services. Full details of the development of the stratification algorithm will be provided in a separate paper. Here we give very brief details on the stratification algorithm and the three derived subgroups. We utilised prognostic information, using the STarT Back tool [25], and clinical information based on the following clinical examination findings: interference with ability to work (including work around the house), pain below the knee, intense leg pain, and sensory changes in the painful leg during neurological examination (loss of or reduced pin prick sensation in a dermatomal distribution in the painful leg). The algorithm allocates patients to one of three subgroups, and each subgroup is matched with a care pathway. We allocated patients to **subgroup 1**, which involves referral to primary care for management options of low treatment intensity, if their total score on the STarT Back tool was less than or equal to 3 out of a possible 9. We used a combination of the STarT Back tool score and a number of findings from the clinical examination described above to direct referral to primary care management options of higher treatment intensity (**subgroup 2**), or to fast-track patients to a specialist spinal opinion and imaging tests (**subgroup 3**). The details of the care pathways for each of the three subgroups, are presented in full later in the text, under the section ‘Stratified care arm: Matched care pathways and their delivery’.

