## Sample size

We have calculated a sample size of 470 participants in total, in order to test for superiority of stratified care compared to non-stratified care. The primary outcome of interest in the SCOPiC trial is time to resolution of symptoms (defined as patient self-report of being ‘completely recovered’ or ‘much better’ compared to baseline (from the 6-point ordinal GPC scale). In our previous trial of stratified care for LBP [23], nearly 60% of patients in total had a clinically important improvement on the GPC scale at 4 and/or 12-month follow up; the absolute difference between arms of that trial at 4 months was 11%. If proportional hazards are to be assumed (i.e. in this case assumed relative rate of ‘resolution’), this difference would equate to an HR in the interval 1.4 - 1.5. Allowing for 20% dropout, a sample size of 470 (235 per treatment arm) is required to detect an HR between 1.4 - 1.5 with 80-90% power (given a two-tailed significance level of 5%), assuming a rate of resolution in excess of 60%, and intra-class correlation (ICC) for physiotherapist effect less than 0.01 (based on estimates from other primary care trials [23, 53], and allowing for a coefficient of variation in physiotherapist cluster size of 0.65 [54]; specifically:an HR of 1.4 in median survival times with 90% power (if all participants in the trial are recovered by 12-month follow-up and ICC for therapist effect is <0.001) (least conservative)an HR of 1.5 in median survival times with 80% power (if 60-65% of participants in the trial are recovered by 12-month follow-up and ICC for physiotherapist effect is 0.01) (most conservative)

An HR above 1 (and correspondingly lower ‘survival’ function) in this context is a positive result in contrast to traditional survival analysis of mortality.

This sample size will also provide more than 80% power to detect a ‘small’ to ‘moderate’ standardised mean difference (effect size) of 0.35 [55] between the two trial arms in a key secondary outcome of physical disability at 12-month follow-up, allowing for an ICC for physiotherapist effect of 0.01.

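### Effectiveness is to be tested in each stratification subgroup, but the only interaction test specified is for disc-related pain, so nothing planned can show whether the effect differs between the three matched pathways

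*Protocol article*

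**What the plan says.** All the relevant text is in the protocol article, mostly under Exploratory subgroup analyses.

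- The section opens with its purpose, which concerns the stratified care model: "A small number of re-analyses of the primary endpoint analysis of time to resolution will be carried out to include testing the effectiveness of stratified". Two factors are named. One is suspected disc-related radicular pain (present or absent). The other is the stratification itself: "and for patients in each of the stratification subgroups (subgroups 1, 2 and 3".
- For the stratification subgroups it offers summaries: "Descriptive statistical summaries will be provided through mean/median time to resolution per treatment arm and per patient subgroup (subgroups 1, 2, 3". These are further broken down by whether disc-related pain is suspected.
- It then states how significance will be tested, naming one model term: "interaction term for the product of group variable (with/without suspected disc-related radicular pain) by treatment arm within the Cox regression model". The group variable is thus defined as disc-related pain only. Stratification group enters that model as a main effect, in the list of covariates: "adjusting for centre, stratification group (stratifying variables), and pain duration".

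No other section supplies an arm-by-subgroup term. Primary analysis and Secondary outcomes analysis both use stratification subgroup as a covariate. The only other interaction, under Assumption checking, is time by arm and serves to examine proportional hazards.

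The Stratification algorithm section explains what the subgroups determine: "The algorithm allocates patients to one of three subgroups, and each subgroup is matched with a care pathway". Randomisation is stratified by centre and subgroup.

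**The concern.** The section promises a test for two factors and specifies one for only one of them. The factor left out is the one that decides what a participant in the experimental arm receives: a brief physiotherapy package, a longer course, or fast-track referral for specialist opinion. Readers will ask whether any benefit belongs to one pathway, and the plan gives the interaction test to disc-related pain instead.

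Two readings are open for subgroups 1 to 3, and each leaves a gap:

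- **Separate re-analyses within each subgroup.** This is the natural sense of re-analysing the primary endpoint for patients in each subgroup. A significant result in one subgroup and a non-significant result in another is not evidence that the two effects differ.
- **Descriptive summaries only.** This follows if the significance-test sentence is read strictly. Subgroups 1 to 3 then have no formal test, which does not fit the announced aim of testing effectiveness in them, and means or medians by arm do not assess a difference in effect.

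What is at stake is any statement in the trial report that stratified care helps one subgroup more than another.

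**Working it through.** **Inputs from the Sample size section.** 470 participants, 20% dropout, so 470 × 0.80 = 376 evaluable; hazard ratio (HR) 1.4 to 1.5; 60-65% resolved in the most conservative scenario and 100% in the least conservative; test level "given a two-tailed significance level of 5" per cent; intra-class correlation (ICC) 0.01 and coefficient of variation of cluster size 0.65 in the conservative case. Allocation is 1:1.

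**Not given, so assumed.** Subgroup shares: equal thirds as the central case, 20% to 50% as the range. Mean physiotherapist cluster size is also not stated.

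**1. The plan's own figure.** Schoenfeld's formula is d = 4(z₁ + z₂)² / (ln HR)².

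- HR 1.4, 90% power: d = 4(1.960 + 1.282)² / 0.3365² ≈ 372 events. With all resolved, N = 372 / 0.80 = 465. Freedman's formula gives 379 events and N = 474. Both agree with 470.
- HR 1.5, 80% power: d = 4(1.960 + 0.842)² / 0.4055² ≈ 191 events. Available events are 376 × 0.60 = 225.6 to 376 × 0.65 = 244.4. With a design effect of 1 + [(1 + 0.65²)m − 1] × 0.01, power at N = 470 is about 80% for a mean cluster size m of about 12-14 (60% resolved) or about 20 (65% resolved).

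So 470 is consistent with its inputs. The figure of 191 is not printed in the article. It is back-calculated, and serves below as the effective number of events after clustering. The range 225.6 to 244.4 ignores clustering.

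**2. Power within one subgroup, if separate tests were done.** Power = Φ(ln HR × √d / 2 − 1.96), true HR 1.5, equal thirds.

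| Total events | Events per subgroup | Power |
|---|---|---|
| 191 | 63.7 | Φ(0.4055 × 7.98 / 2 − 1.96) = 0.37 |
| 225.6 (60%) | 75.2 | 0.42 |
| 244.4 (65%) | 81.5 | 0.45 |

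For subgroup shares of 20% to 50%, without clustering, the range is 28% to 61%. At HR 1.4 with everyone resolved, power per third is 47%.

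**3. Mixed verdicts when the true HR is the same in all three.** P(at least one significant and at least one not) = 1 − p³ − (1 − p)³.

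- p = 0.366: 1 − 0.049 − 0.255 = 0.70
- p = 0.420: 1 − 0.074 − 0.195 = 0.73
- p = 0.448: 1 − 0.090 − 0.168 = 0.74
- HR 1.4, everyone resolved, p = 0.470: 0.75

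With 191 events, splits of 25/50/25 or 40/35/25 give 70-71%, so the result does not hang on equal thirds.

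**4. No effect anywhere.** Three independent 5% tests give 1 − 0.95³ = 14.3% for at least one false positive.

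**5. What the interaction test could do.** Suppose one subgroup has HR 1.5, the other two have 1.0, with equal thirds and no clustering. The non-centrality is (d/4) × Σ(b − b̄)², where d is events per subgroup and b the log hazard ratios. Here Σ(b − b̄)² = 0.4055² × 2/3 = 0.110. With d = 75.2, 81.5 and 125.3 (60%, 65% and 100% resolved), the non-centrality is about 2.06, 2.23 and 3.43. Power on 2 degrees of freedom is 23%, 25% and 36%.

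**The case against.** The strongest reply is that the harm is inferred. The article states no within-subgroup p-value and no 5% threshold for subgroups 1 to 3. Read strictly, its only significance test is the disc-pain interaction, and then the three tests behind the mixed-verdict and 14% figures do not exist. The section is headed "Exploratory subgroup analyses", no objective concerns a difference in clinical effect between subgroups, and asking whether matched care works in a given subgroup is legitimate in itself. A second exploratory model term could also sit in a full protocol or analysis plan that is not shown.

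Much of this stands. A reader might infer that the trial has committed itself to three separate 5% tests. The documents do not say so, and the figures in steps 2 to 4 are conditional on that reading. A reader might also extend the point to the subgroup cost-effectiveness analyses. That does not follow: those are exploratory and work through incremental ratios, planes and acceptability curves, with no significance verdicts to compare.

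What does not stand is treating this as silence left to another document. The section does state its significance test, and restricts it to one of the two factors it has just said will be tested. The exploratory label does not turn within-subgroup results into a comparison between subgroups, and the authors already apply the interaction standard to disc-related pain.

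**Conclusion.** The point holds in a limited form. As written, the section announces testing in subgroups 1, 2 and 3 but specifies no analysis that compares the treatment effect across them. This is true under either reading of how those subgroups will be handled.

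The size of the problem depends on the reading. If within-subgroup p-values were used, then with equal thirds, a common HR of 1.5 and 191 to 244 events in total, each subgroup would have about 37-45% power, and a misleading pattern of mixed significance would arise about 70-74% of the time. The 191 events and the equal thirds are assumptions, not figures from the article. If only descriptive summaries are meant, no such error rate applies, and the fault is that the promised test is missing.

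It would go too far to say that adding the interaction lets the trial settle whether a benefit is specific to one pathway: at 23-36% power in the case examined, a non-significant interaction would not show that the effects are equal. The primary comparison and the sample size are untouched. The correction is worth making because it is cheap and concerns the variable that determines the matched pathway.

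**What to change.** Under Exploratory subgroup analyses, add an arm-by-stratification-subgroup interaction (2 degrees of freedom) to the same Cox model, adjusted for centre, stratification group and pain duration. Report the three subgroup hazard ratios with 95% confidence intervals from that model. State that differences between subgroups are judged on the interaction and not on within-subgroup p-values, and that the result is exploratory.

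The cost is one extra model term and a sentence or two of text, with no new data. The drawback is the low power shown above, so the estimates and their intervals should carry the interpretation.

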#### Secondary outcomes analysis

The analysis will provide between-arm differences in secondary outcomes at 4 and 12 months and provide point and 95% interval estimates from longitudinal linear and logistic mixed effect regression models as appropriate to the outcome data being analysed adjusting for centre, stratification subgroup (1, 2, 3) (stratifying variables) and baseline pain duration. Descriptive summary of mean scores for the two trial arms and difference in mean scores (numerical outcomes) and frequency counts (percentages) along with odds ratios (categorical outcomes) will be presented, with between-arm comparisons being presented in the form of point and 95% interval estimates, alongside p-values for the test of statistical association.

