On a weekly basis, letters inviting patients to the SCOPiC sciatica clinic are mailed to all potentially eligible patients identified from their consultation. The letter and clinic information sheet explains that there is a research study being hosted at the SCOPiC sciatica clinic. Patients are invited to telephone the clinic administrator to make an appointment at the SCOPiC sciatica clinic. During that telephone call, the administrator carries out a brief check for suitability for the clinic. Patients who are receiving or have received care from alternative or complementary HCP practitioners such as osteopaths, chiropractors, acupuncturists or others, are not be excluded but are advised, where possible, to keep co-interventions to a minimum during the treatment phase of the trial. The administrator offers a clinic appointment within 10 working days. A letter is sent to patients to confirm their appointment details, together with a participant information sheet and a baseline questionnaire. Approximately two days before the clinic appointment, a clinic administrator telephones patients to remind them about their appointment and ask those who are interested in taking part in the research to bring their completed questionnaire.

Weekly retrospective GP practice consultation records review may also be used, if needed, as a second method of identifying potentially eligible participants. With this method there is a search for patients for whom the GP has entered one of the agreed Read codes indicating he/she suspects sciatica, so that if GPs overlook or do not have time to complete the electronic ‘pop up’ screen in the consultation, this method will ensure these patients are identified retrospectively and also invited using the same procedures described above. Duplication checks will ensure that the same patient is not invited twice.

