### Clinical outcomes analysis

#### Primary analysis

The primary analysis will compare time to self-reported resolution between stratified care and non-stratified care, on an intention-to-treat basis. A Kaplan-Meier survival analysis will estimate the time from randomisation until first resolution of symptoms. Participants who drop out of the trial through active withdrawal will be censored at the time this occurs (by contrast, participants not responding at any time point will continue to be followed-up until they actively withdraw). This will provide the data for comparing the relative mean and median survival times of the two trial arms. A Cox proportional hazards regression analysis will compare time to resolution between arms by calculation of a hazard ratio (HR) of rates of resolution adjusted for centre, patient stratification group (subgroups: 1, 2, 3) and baseline pain duration. The HR will be presented along with a 95% confidence interval for the HR; a p-value < 0.05 (two-tailed) based on the Wald test statistic will signify rejection of the null hypothesis of no difference in recovery time between the two arms. A statistically significant p-value with HR > 1 would indicate statistically significant shorter time to recovery for stratified care compared to control; a statistically significant p-value with HR < 1 would indicate a (statistical) significantly longer time to recovery for stratified care compared to control. The analysis will account for physiotherapist effect (proportional Cox hazards frailty model).

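### The adjustment list stated for the secondary outcomes leaves out each scored outcome's own baseline value; adding it where it was measured is a free gain in precision

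*Protocol article*

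**What the plan says.** The Secondary outcomes analysis section promises "between-arm differences in secondary outcomes at 4 and 12 months", estimated from "longitudinal linear and logistic mixed effect regression models as appropriate to the outcome data being analysed", and fixes the adjusters by name: "adjusting for centre, stratification subgroup (1, 2, 3) (stratifying variables) and baseline pain duration". These are the same three variables used in the primary Cox model.

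Baseline data exist. Under Identification and invitation of potentially eligible patients, the appointment letter goes out "together with a participant information sheet and a baseline questionnaire". Baseline EQ-5D-5L is named under Health economic outcomes. Baseline leg pain severity or disability is used to select interviewees in the Qualitative study section. The STarT Back score is needed for subgroup allocation, so it is known before randomisation.

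On clustering, the Primary analysis section says "The analysis will account for physiotherapist effect (proportional Cox hazards frailty model". The Sample size section powers disability at 12 months "allowing for an ICC for physiotherapist effect of 0.01". The Secondary outcomes analysis section names no random effects at all.

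**The concern.** The three-variable list suits the primary outcome, because time to first resolution has no baseline value. Most secondary outcomes are scores that can be measured at entry: disability, pain, anxiety and depression, fear of movement, sleep and quality of life. For such scores the starting value is usually the strongest single predictor of the later value. A model without it treats predictable between-person variation as noise.

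Two things follow. The intervals for every scored outcome are wider than the data require. Any chance difference between arms at entry also passes into the estimate, in proportion to the baseline to follow-up correlation. Because the article publishes a specific list, adding baseline after the results are known could look post hoc, so the change belongs before unblinding.

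**Working it through.** **Inputs from the Sample size section.** The section says "a sample size of 470 (235 per treatment arm) is required" and begins the calculation with "Allowing for 20% dropout". That leaves 235 × 0.8 = 188 per arm. The standardised difference is 0.35, the test is two-sided at 5%, the physiotherapist ICC is 0.01 and the coefficient of variation of cluster size is 0.65.

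**Not in the documents, so assumed.** The baseline to follow-up correlation r is taken as 0.3, 0.5 and 0.7. Mean cluster size m is not given and is backed out in step 2.

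**Step 1: reproduce the stated power without clustering.** Power = Φ(0.35 × √(188/2) − 1.96) = Φ(3.393 − 1.960) = Φ(1.433) = 92.4%.

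**Step 2: allow for clustering.** The design effect is DE = 1 + ((1 + 0.65²)m − 1) × 0.01.
- The most conservative primary scenario (hazard ratio 1.5, 80% power) needs 191 events by Schoenfeld's formula.
- With 376 analysed and 60–65% resolved there are 225.6 to 244.4 events.
- The implied DE is therefore 225.6/191 = 1.18 to 244.4/191 = 1.28, or m of about 13 to 20.
- Dividing 188 by 1.18 and by 1.28 gives power of about 88% and 85%.

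The stated figure of more than 80% reproduces, with no reliance on baseline adjustment.

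**Step 3: effect of adding baseline (linear models).** Residual variance is multiplied by 1 − r² and interval width by √(1 − r²), if the covariates already listed explain none of the same variance.

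| Assumed r | Variance removed | Width factor |
|---|---|---|
| 0.3 | 9% | 0.95 |
| 0.5 | 25% | 0.87 |
| 0.7 | 51% would remain (49% removed) | 0.71 |

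At r = 0.5 the gain is worth 1/0.75 = 1.33 times the sample, about a third more participants. If the design effect is unchanged, power for disability at DE 1.18 to 1.28 rises from 88–85% to about 95–93%. For example, at DE 1.18 the effective number per arm is 188/(1.18 × 0.75) = 212, and Φ(0.35 × √(212/2) − 1.96) = 95%.

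**Step 4: chance imbalance.** With 188 per arm, one standard error of the difference in baseline means is √(2/188) = 0.10 SD. At r = 0.5 an imbalance of that size moves the unadjusted estimate by about 0.05 SD, against a target of 0.35. This is the same variance seen from another side, not a further loss.

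**Step 5: why these are best cases.** The stratification algorithm uses the STarT Back score, work interference, intense leg pain, pain below the knee and sensory findings. Adjusting for subgroup therefore removes some of the variation that baseline scores would explain. How much cannot be computed from the article.

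**The case against.** The case for leaving the text alone has real force. A journal article condenses, and an analysis plan not shown may add baseline. A longitudinal model could also hold baseline as a repeated measurement, although the section names only 4 and 12 months. Subgroup already carries some severity, the correlations are assumed, and only secondary outcomes are affected. Table 1 is not visible, so a baseline for anxiety and depression, fear of movement and sleep is presumed, not shown. All of this stands and limits the size of the point. It does not remove it, because the article states an explicit list and that list is a poor choice for scored outcomes.

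A reader might go further and infer that the secondary analyses ignore physiotherapist clustering, so that a nominal 5% test really runs at about 7.1–8.3%. The documents do not support this:
- The models are mixed-effect with random effects unlisted. The primary analysis states its frailty term in a sentence apart from the same three covariates, so absence from the covariate list excludes nothing.
- The disability power statement allows for the physiotherapist ICC, which suggests that the effect is intended.
- The error rate comes from 2(1 − Φ(1.96/√DE)) with the back-calculated DE of 1.18–1.28. Over assumed cluster sizes of 5 to 30 it would be 5.7–10.0%.
- It also uses the upper end of the ICC range in the Sample size section. At an ICC of 0.001 and m of 13 to 20, DE is about 1.02–1.03 and the rate about 5.2–5.3%.

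The two omissions would also act in opposite directions: leaving out baseline widens intervals, whereas ignoring clustering would narrow them. They should not be merged into one complaint.

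**Conclusion.** The point holds as a free improvement. The stated list omits the baseline value of the scored outcomes. The result is not biased by design, but it is less precise than the data allow, and chance imbalance stays in the estimate. The best-case width factors of 0.95, 0.87 and 0.71 rest on assumed correlations of 0.3, 0.5 and 0.7 and on the listed covariates sharing none of that variance, so the true gain is likely to be smaller. They apply to the linear models. In the logistic models, adding baseline also changes which odds ratio is estimated, so the width factor does not carry over directly.

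No stated figure is wrong, and the primary analysis is untouched. The physiotherapist effect in the secondary models is unstated, not excluded, so it is a matter for confirmation and not a defect.

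**What to change.** In the Secondary outcomes analysis section, or in the analysis plan before unblinding, add the baseline value of the outcome wherever it was measured. Name one form in advance: baseline as a covariate with a time interaction, or baseline as the first repeated measurement with arm means constrained to be equal. Global perceived change and satisfaction with care have no natural baseline and stay as planned.

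In the same place, confirm that the mixed models carry a physiotherapist random effect consistent with the primary analysis and the sample size calculation.

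The cost is a sentence or two. No further data are needed for outcomes already measured at baseline, and the sample size does not change.
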